# 0 PROTOCOL SYNOPSIS

## 0.1 STUDY SCHEME

Figure 1

Infants with atopic dermatitis at the age of 7–13 weeks

N=650

Registration and Randomization

Conventional treatment group, n=325

Standard treatment based on clinical practice guidelines for the management of atopic dermatitis 2016 (1)

(Reactive method)

Aggressive intervention group, n=325

Early aggressive treatment with topical corticosteroids

(Proactive method)

## 0.2 PURPOSE

To test the superiority of aggressive intervention to prevent food allergy over conventional treatment in infantile atopic dermatitis (AD) by a randomized controlled trial (RCT).

## 0.3 STUDY DESIGN

This study is designed as a multicenter, investigator-blinded, randomized, parallel group controlled trial.

## 0.4 PARTICIPANTS

Infants (7–13 weeks old) who develop an itchy rash within the previous 28 days and receive a diagnosis of AD by a dermatologist, based on the U.K. Working Party’s diagnostic criteria

## 0.5 PRIMARY ENDPOINT

Presence of oral food challenge-proven IgE-mediated hen’s egg allergy at 28 weeks of age

## 0.6 STUDY PROCEDURE

**0.6.1 Aggressive intervention group: Early aggressive treatments with topical corticosteroids**

**(Proactive method)**

Basic whole-body treatment

Participants will be followed as described below and administered basic whole-body treatment, except for scalp.

Emollients

|  | Whole body except scalp |
| --- | --- |
| Registration day (Day 0) of the study  to 28 weeks of age | Hirudoid^®^ Soft ointment  every day  twice a day |

Topical corticosteroids

|  | Face | Body except scalp and face |
| --- | --- | --- |
| Registration day (Day 0) to Day 14 of the study | Almeta^®^ ointment  every day  twice a day | Rinderon^®^-V ointment  every day  twice a day |
| Day 15 of the study  to 28 weeks of age | Almeta^®^ ointment  two days per week  twice a day | Rinderon^®^-V ointment  two days per week  twice a day |

Additional skin rash treatment

Participants are to apply TCSs as additional treatment as described below:

| Face | Body except scalp and face | Scalp |
| --- | --- | --- |
| Day 15 of the study  to 28 weeks of age | Day 15 of the study  to 28 weeks of age | Day 15 of the study  to 28 weeks of age |
| Almeta^®^ ointment  every day until rash remission  twice daily | Rinderon^®^-V ointment  every day until rash remission  twice a day | Rinderon^®^-V lotion until rash remission  twice a day |

**0.6.2 Conventional treatment group: Standard treatment based on the Guidelines for the Management of Atopic Dermatitis (2016) (1) (Step-up reactive method)**

Basic whole-body treatment

Participants will be followed as described below and administered basic whole-body treatment, except for scalp.

|  | Whole body except scalp |
| --- | --- |
| Registration day (Day 0) of the study  to 28 weeks of age | Hirudoid^®^ Soft ointment  every day  twice a day |

Additional skin rash treatment

Participants are to apply TCSs as additional treatment as described below:

| Area | Face | | Body except scalp and face | | | Scalp |
| --- | --- | --- | --- | --- | --- | --- |
| Severity of skin rash | Less mild | Mild, moderate, and severe | Less mild | Mild and moderate | Severe | Any severity |
| Registration day (Day 0) of the study  to 28 weeks of age | Without additional treatment | Almeta^®^ ointment  every day until rash remission  once a day | Without additional treatment | Almeta^®^ ointment  every day until rash remission  once a day | Rinderon^®^-V ointment  every day until rash remission  once a day | Rinderon^®^-V lotion until rash remission  once a day |

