**Sensitization**

Sensitization is defined as a serum specific IgE titer of 0.35 UA/mL and over.

**Adherence index** An adherence index is determined by the percentage of TCSs applied in accordance with the protocol (days of actual TCS application/days of TCS application required in the study protocol). Good adherence is defined as an adherence index of 70% or more. Poor adherence is defined as an adherence index of less than 70%.

**Age in days and age in weeks** Birth day is defined as an age of 0 days. Age in weeks is defined as listed below.

| Age in weeks | | Age in days | | |  |
| --- | --- | --- | --- | --- | --- |
| 1 | week | 0 | – | 6 | days |
| 2 | weeks | 7 | – | 13 | days |
| 3 | weeks | 14 | – | 20 | days |
| 4 | weeks | 21 | – | 27 | days |
| 5 | weeks | 28 | – | 34 | days |
| 6 | weeks | 35 | – | 41 | days |
| 7 | weeks | 42 | – | 48 | days |
| 8 | weeks | 49 | – | 55 | days |
| 9 | weeks | 56 | – | 62 | days |
| 10 | weeks | 63 | – | 69 | days |
| 11 | weeks | 70 | – | 76 | days |
| 12 | weeks | 77 | – | 83 | days |
| 13 | weeks | 84 | – | 90 | days |
| 14 | weeks | 91 | – | 97 | days |
| 15 | weeks | 98 | – | 104 | days |
| 16 | weeks | 105 | – | 111 | days |
| 17 | weeks | 112 | – | 118 | days |
| 18 | weeks | 119 | – | 125 | days |
| 19 | weeks | 126 | – | 132 | days |
| 20 | weeks | 133 | – | 139 | days |
| 21 | weeks | 140 | – | 146 | days |
| 22 | weeks | 147 | – | 153 | days |
| 23 | weeks | 154 | – | 160 | days |
| 24 | weeks | 161 | – | 167 | days |
| 25 | weeks | 168 | – | 174 | days |
| 26 | weeks | 175 | – | 181 | days |
| 27 | weeks | 182 | – | 188 | days |
| 28 | weeks | 189 | – | 195 | days |

**Nutrition** Nutrition methods are defined as follows:

Breastfeeding: ingesting maternal breast milk

Regular cow’s milk formula feeding: ingesting regular cow’s milk formula

Hypoallergenic infant formula feeding: ingesting partially hydrolyzed and extensively hydrolyzed formulas

Mixed feeding: ingesting by both breastfeeding and infant formula feeding

Weaning food: ingesting semi-solid and/or solid foods

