# 6 STUDY ASSESSMENTS (Observation, test, and evaluation)

## 6.1 ASSESSMENT SCHEDULE

|  | Study treatment start | Study period | | | |
| --- | --- | --- | --- | --- | --- |
| Visit | 1 | 2 | 3 | 4 | 5 |
| Study duration | Entry  (Day 0) | 2 weeks after entry  (Day 14) | 4 weeks after entry  (Day 28) | 8 weeks after entry  (Day 56) | 28 weeks of age |
| Visit windows |  | ±6 days | ±7 days | ±7 days | ±14 days |
| Informed consent | X |  |  |  |  |
| Background information | X |  |  |  |  |
| Nutrition | X | X | X | X | X |
| Living environment | X | X | X | X | X |
| Body height | X | X | X | X | X |
| Body weight | X | X | X | X | X |
| Oral food challenge test  (hen’s egg) |  |  |  |  | X |
| IgE-mediated FA  by interview | X | X | X | X | X |
| Wheeze | X | X | X | X | X |
| Total IgE, egg white, ovomucoid, milk, wheat soy, peanut, and Ara h2-specific IgE and IgG4 antibodies in serum | X |  |  |  | X |
| EASI  by blinded physician | X | X | X | X | X |
| POEM  by caregivers |  | ✔ | ✔ |  | Every week |
| Disease-free days of AD |  | X | X | X | X |
| Amount of emollients and TCSs including rescue medication usage |  | X | X | X | X |
| Days of applying emollients and TCSs including rescue medication usage |  |  |  | Daily |  |
| IDQoL and DFI scores | X | X | X | X | X |
| Salivary cortisol |  | X | X | X | X |
| Concomitant therapy | X | X | X | X | X |
| Adverse events |  | X | X | X | X |
| Amount of emollients and TCSs used |  | X | X | X | X |

Measurement of specific IgG4 antibody titer is carried out at the Institute of Enzyme Research, University of Tokushima, and salivary cortisol is measured at the Center for Environmental Risk Research, National Institute for Environmental Studies (Supplement 12). The total IgE antibody titer and the specific IgE antibody titers are measured by the ImmunoCAP method provided by health insurance.

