## 8.2 SECONDARY ENDPOINTS

EFFICACY ENDPOINTS

1. Food challenge test scores at the age of 28 weeks
2. Total IgE antibody titer in serum at the age of 28 weeks
3. Egg white, ovomucoid, milk, soy, wheat, and peanut-specific IgE antibody titers in serum at the age of 28 weeks
4. Egg white, ovomucoid, milk, soy, wheat, and peanut-specific IgG4 antibody titers in serum at the age of 28 weeks
5. Eczema Area and Severity Index (EASI) scores at 2, 4, and 8 weeks after study entry and at the age of 28 weeks
6. Patient Oriented Eczema Measure (POEM) scores weekly through the study
7. Percentage of disease-free days throughout the study
8. Dose of rescue medication used throughout the duration of the study
9. Infants’ Dermatitis Quality of Life Questionnaire (IDQoL) at 2, 4, and 8 weeks after study entry and at 28 weeks of age
10. Family Impact of Childhood Eczema Questionnaire (DFI) at 2, 4, and 8 weeks after study entry and at 28 weeks of age
11. Cumulative incidence of IgE-mediated FA assessed by a doctor’s interview during the study
12. Cumulative incidence of wheezing assessed by a doctor’s interview during the study

Justification for secondary endpoints (efficacy)

(1) Scoring of the food challenge test has already been recommended in the American Academy of Allergy, Asthma & Immunology – European Academy of Allergy and Clinical Immunology PRACTALL consensus report (65).

(2) (3) To evaluate allergy sensitization

(4) To evaluate immune tolerance against hen’s egg

(5) (6) To evaluate the activity and severity of AD

(7) (8) To evaluate the disease control

(9) (10) To evaluate the QoL

(11) To evaluate the prevalence of other IgE-mediated FA except hen’s egg

(12) To evaluate the prevalence of signs related to asthma

SECONDARY ENDPOINTS (SAFETY)

1. Serious adverse events
2. Adverse drug reactions
3. Salivary cortisol concentrations at 2, 4, and 8 weeks after study entry and at the age of 28 weeks
4. Body weight and body height at the age of 28 weeks

Justification for secondary endpoints (safety)

(1) (2) To evaluate safety of the study drugs

(3) To evaluate the effect on adrenal function by adverse drug reactions to TCSs

(4) To evaluate the effect of adverse drug reactions to TCSs on growth

ADHERENCE EVALUATION

(1) TCS adherence index in accordance with the protocol

(2) Dose of TCS used during the study

Justification for adherence evaluations

(1)(2) To evaluate adherence to the protocol

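### The adherence index counts steroid days, not applications, so per treated site 'good' adherence can mean as little as 35% of required applications in the twice-daily arm, against 70% in the once-daily arm

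*Protocol*

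**What the plan says.** Treatment frequency differs by arm. In Protocol sections 0.6.1 and 5.6.3 the aggressive arm applies steroid twice on every steroid day. For the body this is "Rinderon^®^-V ointment every day twice a day" from Day 0 to Day 14 and "Rinderon^®^-V ointment two days per week twice a day" from Day 15; additional rash treatment is also twice a day. In sections 0.6.2 and 5.6.4 the conventional arm applies it once a day wherever it is given, for example "Almeta^®^ ointment every day until rash remission once a day".

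Section 3 (Adherence index) has one definition for both arms. It opens: "An adherence index is determined by the percentage of TCSs applied in accordance with the protocol". The formula in parentheses is "days of actual TCS application/days of TCS application required in the study protocol". The cut follows: "Good adherence is defined as an adherence index of 70% or more". Anything below 70% is poor.

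The section 6.1 schedule has a row for "Days of applying emollients and TCSs including rescue medication usage", and section 6.2 also lists days used. Section 5.6.1 has families record how topical medicines were applied in a treatment diary and bring back containers and leftovers. Section 8.2 lists "TCS adherence index in accordance with the protocol" as the first adherence evaluation and the dose of TCS used as the second; both are there to assess adherence to the protocol.

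**The concern.** The formula has no term for applications per day. In the conventional arm one application at a site completes that site's day. In the aggressive arm one application is half of what the day requires, yet on the plain reading it earns the full day. Frequency of application is one of the features that separate the two regimens, so an infant who regularly misses the second application moves towards the comparator's frequency and is still recorded as fully adherent.

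What is at stake is interpretation. If the trial finds a small or null effect, readers will ask whether the aggressive regimen was actually given. A high proportion with good adherence would suggest that it was, although the index cannot distinguish full from half daily treatment.

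**Working it through.** The 70% cut is a definition, so there is no derived figure to reproduce. The check asks what it means in applications.

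**Inputs**
- Index = days of application ÷ required days; cut 0.70 in both arms (section 3).
- Required applications per site on a steroid day: k = 2 in the aggressive arm (0.6.1, 5.6.3) and k = 1 in the conventional arm (0.6.2, 5.6.4).
- Age at entry 7–13 weeks is days 42–90, and 28 weeks of age is days 189–195 (age table, section 3). I use the midpoint, day 192, as the end.
- Assumption: a day with at least one application counts as a day of application.

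**Floor at the cut, per treated site**
- Lowest share of required applications = 0.70 × 1/k.
- Aggressive arm: 0.70 × 1/2 = 35%. If both applications are made on each counted day, the share is 70%, so the range is 35% to 70%.
- Conventional arm: 0.70 × 1/1 = 70%.

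**Worked example, aggressive arm, no flares**
- Required days = 15 + (T − 15) × 2/7, where T is days from entry to the end and 15 covers Day 0 to Day 14. Required applications per site = 2 × required days.

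| Entry (day of age) | T | Required days | Required applications |
|---|---|---|---|
| 42 | 150 | 15 + 135 × 2/7 = 53.6 | 107 |
| 66 | 126 | 15 + 111 × 2/7 = 46.7 | 93 |
| 90 | 102 | 15 + 87 × 2/7 = 39.9 | 80 |

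- Once-daily use on all required days, entry at day 66: index 46.7/46.7 = 100%; applications 46.7/93.4 = 50%.
- Once-daily use on 70% of required days: 0.70 × 46.7 = 32.7 days; 32.7/93.4 = 35%.
- The 50% and 35% do not depend on entry age. Nor do they change with flares or with the extension of daily treatment to Day 28 in section 5.6.3, because every aggressive-arm steroid day carries two applications per site.

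**Several sites**
- Face, body and scalp are prescribed separately. If any application makes a counted day, a conventional-arm infant with rash at all three sites who is treated at one can reach the cut with 0.70 × 1/3 = 23% of required site-applications.
- An aggressive-arm infant needing face and body twice daily, but treated at one site once, can reach it with 0.70 × 1/4 = 17.5%.
- So the 35% and 70% hold per treated site and are not whole-infant floors in either arm.

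**Same once-daily infant under the alternatives**
- Applications made ÷ applications required: 50%, poor.
- Counting only days with all required applications: 0 of 46.7 days, 0%, poor.

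**The case against.** The strongest objection is that the definition opens by speaking of steroid applied as the protocol directs. A day with one of two applications is arguably not such a day. If only complete days counted, 70% would mean at least 70% in both arms and the asymmetry would vanish. That reading is possible, but the formula that puts the phrase into operation refers to days of actual application, and nothing in the protocol says how a half-treated day is scored. A statistical analysis plan, not available here, might say so; but formula and cut are already fixed in the protocol, and an analysis plan that simply follows them inherits the problem.

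Second, the dose of TCS used is a companion measure, and skipping the second application would tend to lower it. This stands in part, and it would be wrong to say that the adherence evaluation as a whole is blind. But the check is indirect: rash extent and rescue use also move the amount, no required quantity is stated to divide it by, and it does not change the good/poor label.

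Third, the diary may already record each application. Its form is not shown, so whether a new field is needed is open.

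A reader might also infer that the error runs in one direction and biases adherence comparisons in favour of the aggressive arm. The documents do not support that. Missing a second application can be hidden only in the aggressive arm, but partial treatment across sites can inflate the index in both, and the frequency of either is unknown. No between-arm test of adherence is specified.

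**Conclusion.** The point holds in limited form. On the plain reading of section 3, the same 70% cut corresponds per treated site to a floor of 35% of required applications in the aggressive arm and 70% in the conventional arm, and once-daily use in the aggressive arm scores 100% at half the required applications. This rests on any application making a counted day. The 35% is a worst case, with every counted day half-treated and exactly 70% of days counted; it should not be read as expected adherence.

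Nor should it be read as a threat to the efficacy result. The primary analysis on the Full Analysis Set (9.3.2) does not use the index, and section 9.2 does not tie the Per Protocol Set to it. The effect is confined to reported good/poor adherence and to how a small or null effect is explained. The net direction and size of any bias cannot be determined from the protocol. The definition should be corrected, as a point of secondary weight.

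**What to change.** In section 3, adopt one of two definitions and keep the 70% cut:

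- count a day as a day of application only if all applications required that day were made; or
- define the index as applications made on required days divided by applications required, and say how sites are counted. Since sections 5.6.3 and 5.6.4 allow re-application after washing or wiping, cap each day's count at the number required.

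Take the counts from the treatment diary (5.6.1). If it does not record applications per day, add that field to the diary and the eCRF. Where only days are available, report the result as a day-based index and do not label it good adherence.

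The cost is a sentence or two of definition, possibly one field with slightly more work for parents and sites, and perhaps a less favourable aggressive-arm figure. No treatment rule changes.

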## 0.7 ANTICIPATED NUMBER OF PARTICIPANTS AND STUDY DURATION

1. The anticipated number of participants is 650: Aggressive intervention group, n=325 and conventional treatment group, n=325.
2. Duration of the study registration will be 2 years after IRB approval.
3. Duration of the study intervention will be 3 years after IRB approval.

| US | United States of America |
| UMIN-CTR | University Hospital Medical Information Network |

# 1 BACKGROUND

## 1.1 ATOPIC DERMATITIS

1.1.1 ATOPIC DERMATITIS

AD is a disease with repeated exacerbation and remission, that is chiefly characterized by eczema with itch, and it is mostly exhibited by patients with atopic diathesis (personal or family history of bronchial asthma, allergic rhinitis, and conjunctivitis, and/or AD and/or predisposition to overproduction of immunoglobulin E (IgE) antibodies) **(1). Severely affected children have severe sleep disturbance and the condition places a heavy burden on daily life. Epidermal barrier dysfunction plays an important role in AD pathophysiology.** The skin barrier consists of tight junctions of the stratum layer, filaggrin protein with keratin filaments of keratinocytes, desmosomes connecting keratinocytes, natural moisturizing factors with water holding water intracellular lipids with ceramides, sebaceous membranes of outlayer and so on. Filaggrin partially forms the epidermal barrier and filaggrin loss-of-function mutations were found to be more common among patients with AD compared with unaffected populations (2, 3). Reduced filaggrin expression was also found in patients with AD who were not carriers of known filaggrin mutations (4). Two randomized controlled trials (RCTs) were performed to investigate whether protecting the skin barrier with a moisturizer applied at the beginning of the neonatal period would prevent development of infantile AD. These studies demonstrated that application of a moisturizer during early life reduced the incidence of AD/eczema in infants (5, 6). Inflammation on the skin and allergic sensitization is also suggested as a mechanism of AD. Once skin barrier dysfunction occurs, allergens and bacterial toxins from outside the skin penetrate the skin barrier. Langerhans cells extend dendrites through the tight junctions and capture antigens from outside the tight junction barrier (7, 8). It was suggested that T-helper type 2 cells shift allergic sensitization in patients with AD, which might be initiated by the external antigen uptake by Langerhans cells in an inflamed epidermal layer. Various immune cells such as sensitized T cells release cytokines that cause allergic inflammation of the skin. Skin inflammation induces itch on the skin and the itch-scratch cycle reduces skin barrier function.

1.1.2 ATOPIC DERMATITIS EPIDEMIOLOGY

A systematic review of international trends in AD suggested that the prevalence of atopic eczema is increasing in Africa, eastern Asia, western Europe, and parts of northern Europe (e.g., the UK) (9). According to a Japanese national survey, the prevalence of infants at the age of 6 months with AD or a suspected history of AD was about 25% (10). Rudikoff *et al.* reported that onset of AD is within the first year of life in 60% of patients (11). A cohort study in Stockholm demonstrated that children with single or double parental atopic history developed AD with 37.9% or 50.0%, respectively, at 4 years of age (12) and most children with AD have a family history of atopy. The allergic march concerns the development of AD and concomitant sensitization to food and aeroallergens in early childhood, progressing to asthma and allergic rhinitis in later childhood or adult life (13). Of 1-year-old children who ever received a diagnosis of AD, 19.3% had a food allergy (FA) at 3 years of age in the T-CHILD birth cohort study in Japan (14).

1.1.3 ATOPIC DERMATITIS MANAGEMENT

According to the Japanese guidelines for AD (1), there are recommendations for basic treatments, namely, investigate and treat causes and exacerbating factors, correct skin dysfunctions (skin care), and use pharmacotherapy; this is similar to guidelines in other countries.

<Investigate and treat causes and exacerbating factors>

Although the exacerbating factors of AD are different among patients because of age and life environment, patients are encouraged to eliminate factors such as the effects from sweat, house dust mites, pets, *Staphylococcus aureus*, and dryness. Patients are encouraged to control the home environment, reducing these exacerbating factors.

<Skin care>

Skin care is needed to eliminate exacerbating factors such as *S. aureus*, sweat, irritants, and allergens and keep the skin clean. In addition, emollients are applied to maintain the skin barrier function.

<Pharmacotherapy>

Topical corticosteroids (TCSs) and tacrolimus ointments are the mainstream of pharmacotherapy to suppress skin inflammation associated with AD. Tacrolimus has been officially approved for patients 2 years of age and older in Japan.

TOPICAL CORTICOSTEROIDS (TCSs)

TCSs are medications to control inflammation on the skin and are the most frequently used as pharmacotherapy for AD. In Japan, TCS potency has five categories: strongest, very strong, strong, medium, and weak (Table 1). However, TCS potency is not the same in every country. TCS potency in the US has seven categories (15) and that in the UK has four categories (16). The potency of mometasone furoate, betamethasone valerate, and alclometasone dipropionate in Japan, the US, and the UK is summarized in Table 2. For applying TCSs, the finger-tip unit (FTU) is used as an index of the external dose. One FTU is a dose equivalent to approximately 0.5 g of ointment, which can cover the area of two palms of an adult (2% of the body surface area) (17). The approach for using TCSs in AD is either reactive or proactive management (Figure 2) (18, 19). Reactive management is when TCSs are administered only when the rash worsens. Proactive management is applying anti-inflammatory TCS therapy intermittently even after the skin clears to suppress subclinical inflammation of the skin in AD patients. Proactive management is preferable for patients with moderate or severe AD, because reactive management of flare-ups is not always successful to control AD symptoms. An RCT by Hanifin *et al.* compared proactive management using fluticasone propionate cream 0.05% (twice per week) with its vehicle base to reduce the risk of relapse in subjects aged 3 months to 65 years with stabilized AD (20). Pediatric patients were 8.1 times less likely to have an AD relapse (95%CI: 4.3, 15.2; *p*<0.001) and proactive management was considered to reduce the risk of flare-ups. Fukuie *et al.* conducted an RCT to investigate whether, when compared with reactive therapy, 1-year proactive therapy would stabilize AD symptoms (21). They measured serum TARC as a biomarker of AD severity and prevented subsequent sensitization to aeroallergens in children aged 3 to 90 months with AD. At the study end, the SCORAD index was significantly lower in the proactive treatment group compared with the reactive treatment group. In addition, Fukuie *et al.* performed a 2-year retrospective cohort study of patients with moderate to severe AD to investigate whether proactive management changes serum IgE level compared to reactive management (22). Serum total IgE titer was significantly decreased in the proactive treatment group compared with the reactive treatment group (2442 IU/mL vs. 2081 IU/mL; *p*<0.01). In addition, the serum egg white-specific IgE level decreased significantly during follow-up (60.0 IU/mL vs. 36.6 IU/mL; *p*=0.004). In a case control study, infants with early proactive management (beginning at ≤4 months old) had a lower prevalence of egg allergy compared to infants with later proactive management (beginning at ≥5 months) at the age of 18 months (9.1% vs. 24.2%) (23). Previously published results suggest that proactive management might be effective for reducing eczema flare-ups, and for preventing development of allergic sensitization. Thus, early proactive management for infantile AD may reduce the risk of FA.

SAFETY OF TOPICAL CORTICOSTEROIDS

TCSs are topical anti-inflammatory agents and they are safer than systemic steroids administered via an oral or intravenous route. Absorption of TCS in the skin is considered to depend on many factors such as molecular weight of TCS, cream or ointment bases, application amount, potency of TCS, application period, and age. Cutaneous side effects include telangiectasias, skin atrophy, skin striae, focal hypertrichosis, acne-like eruptions, rosacea-like eruptions, folliculitis, and so forth (24, 25). In an observational study in the US, children with moderate or severe AD did not show adrenal suppression although they had used TCSs for more than several years since infancy (26). Fukuie *et al.* performed rapid ACTH stimulation tests for eight children in the proactive group and four children in the reactive group at 3 months after starting the study intervention and found that no children showed adrenal suppression (21). However, Hanifin *et al.* demonstrated that 2/44 children in the proactive group had adrenal suppression in the RCT (20). Children are more susceptible to steroids than adults and, therefore, their treatment should be carefully considered.

Table 1. TCS potency categories in Japan (1)

| Potency | Generic name and strength | Brand name |
| --- | --- | --- |
| Strongest | 0.05% Clobetasol propionate | Dermovate^®^ |
|  | 0.05% Diflorasone diacetate | Diflal^®^, Diacort^®^ |
| Very strong | 0.1% Mometasone furoate | Flumeta^®^ |
|  | 0.05% Betamethasone butyrate propionate | Antebate^®^ |
|  | 0.05% Fluocinonide | Topsym^®^ |
|  | 0.064% Betamethasone dipropionate | Rinderon^®^-DP |
|  | 0.05% Difluprednate | Myser^®^ |
|  | 0.1% Amcinonide | Visderm^®^ |
|  | 0.1% Diflucortolone valerate | Texmeten^®^, Nerisona^®^ |
|  | 0.1% Hydrocortisone butyrate propionate | Pandel^®^ |
| Strong | 0.3% Deprodone propionate | Eclar^®^ |
|  | 0.1% Dexamethasone propionate | Methaderm^®^ |
|  | 0.12% Dexamethasone valerate | Voalla, Zalucs^®^ |
|  | 0.1% Halcinonide | Adcortin^®^ |
|  | 0.12% Betamethasone valerate | Betnevate^®^, Rinderon^®^-V |
|  | 0.025% Fluocinolone acetonide | Flucort^®^ |
| Medium | 0.3% Prednisolone valerate acetate | Lidomex^®^ |
|  | 0.1% Triamcinolone acetonide | Ledercort^®^ |
|  | 0.1% Alclometasone dipropionate | Almeta^®^ |
|  | 0.05% Clobetasone butyrate | Kindavate^®^ |
|  | 0.1% Hydrocortisone butyrate | Locoid^®^ |
| Weak | 0.1% Dexamethasone | Glymesason^®^, Eurason^®^ |
|  | 0.5% Prednisolone | Prednisolone^®^ |

Table 2. Comparison of TCS potency in Japan, the US, and the UK

| TCS | Japan (Ⅰ-Ⅴ) | US (Ⅰ-VII) | UK (Ⅰ-IV) |
| --- | --- | --- | --- |
| Fulumeta^®^  (Mometasone furoate) | Very strong (II) | High (II) | Potent (II) |
| Rinderon^®^-V  (Betamethasone valerate) | Strong (III) | Medium (III) | Potent (II) |
| Almeta^®^  (Alclometasone dipropionate) | Medium (IV) | Low (IV) | Moderate (III) |

Figure 2. Reactive and proactive management plan for AD (19)

